## Abstract

**Background:**

Dry eye syndrome is a frequent complication of refractive surgery. Acupuncture has been widely used to alleviate the associated symptoms. However, the use of acupuncture for patients who suffer from dry eye syndrome following refractive surgery has certain drawbacks. This pilot study aims to evaluate the efficacy of acupuncture treatment in treating the signs and symptoms of dry eye syndrome after refractive surgery.

**Methods/design:**

Forty participants will be randomly assigned to the acupuncture plus usual care group or the usual care control group. The acupuncture plus usual care group will undergo treatments on seventeen acupuncture points, three times per week for four weeks. The control group will receive only usual care during the same period. The primary outcomes will be scores on the Ocular Surface Disease Index (OSDI) and the results of examinations at 1, 3, 5, and 13 weeks. The secondary outcomes will be Tear Film Break-up Time (TBUT), as well as scores on the Schirmer-I test, visual analog scale (VAS), and quality of life (QOL) questionnaire for the self-assessment of ocular discomfort. Digital photographs will be taken to document the pattern of fluorescein staining observed on the corneal surface. The results of the Schirmer-I test, TBUT, and fluorescein-stained corneal surface digital photographs will be assessed at the screening and at week 13. VAS scores will be assessed at the screening, as well as at 1, 3, 5, and 13 weeks. QOL will be evaluated at 1, 3, 5, and 13 weeks.

**Discussion:**

This trial will provide primary data with which to investigate the clinical effectiveness and safety of acupuncture treatment for dry eye syndrome after refractive surgery.

**Trial registration:**

Current Controlled (Identifier: KCT0000727)

## Background

Refractive surgery involves the use of an excimer laser to ablate the cornea, thereby correcting the patient’s refractive error [1]. Various types of refractive surgery have been developed: photorefractive keratectomy (PRK), laser *in situ* keratomileusis (LASIK), and laser-assisted subepithelial keratomileusis (LASEK). Since the excimer laser was first used to reshape the cornea, the surgery has been performed on approximately 100,000 patients in Korea each year [2]. Various other ophthalmological advancements have improved the safety, efficacy, and predictability of surgical outcomes [3,4]. Despite these advances, however, certain limitations and complications remain. These include infection, ectasia, diffuse lamellar keratitis, subepithelial haze, dry eye, epithelial ingrowth, and the development of a button-hole flap [5].

Up to 94.8% of patients experience dry eye symptoms after refractive surgery [6]. The National Evidence-based healthcare Collaborating Agency (NECA) reported that 17% of refractive surgery patients later suffer from chronic dry eye [2].

The use of artificial tears and lifestyle modifications are currently the most common approaches to management. However, the preservatives in artificial tears may exacerbate ocular surface inflammation, and the safety of anti-inflammatory treatment is not well established [7,8]. In this context, complementary and alternative medicine can do much to alleviate the patient’s pain [9-14]. This pilot study focuses on the efficacy of acupuncture in relieving the signs and symptoms of chronic dry eye syndrome after refractive surgery.

## Methods/design

### Study design

This is a randomized, controlled pilot trial. All participants will be randomly allocated to the acupuncture plus usual care group (n = 20) or the usual care control group (n = 20). The acupuncture plus usual care group will receive 12 sessions of treatment over a four-week period. The study design is depicted in Figure 1.

**Figure 1 F1:**
[figure not shown]
**Study flow chart.** a: 5 week (4 weeks after visit 2 + within 3 days), b: 13 week (12 weeks after visit 2 + within 3 days).

### Ethics

This study was approved by the Institutional Review Board (IRB) at the Oriental Hospital of Daejeon University, Korea (IRB approval number: djomc-98-1) and was registered with the Clinical Research Information Service at the Korea National Institute of Health (KCT0000727). Each participant will provide written informed consent prior to participation in the study.

### Recruitment

Participants will be recruited through advertisements in the local newspaper, distributed leaflets, the university homepage, and posts on notice boards. At the first (screening) visit, each participant’s demographic information (including ocular pathologies and current/prior use of medications and/or lubricant eye drops) will be recorded. Study participants who have experienced dry eye symptoms for at least 24 months after undergoing refractive surgery will be enrolled in the study. Patients will be included only if their ocular discomfort is rated ≥ 40 on the visual analog scale (VAS) and if the associated ophthalmological test results are abnormal (that is, Tear Film Break-up Time (TBUT) ≤ 10 seconds, ≤ 10 mm/5 minutes on the Schirmer-I test) [15] (Table 1).

**Table 1 T1:** Inclusion and exclusion criteria

Inclusion criteria	1. Men and women, 18 to 65 years old
	2. Dry eye syndrome in one or both eyes (ICD-10:H04.1) with:
	2-1. Refractive surgery within 24 months and dry eye symptoms (for example, ocular itching, foreign body sensation, burning, pain and dryness, visual disturbance, ocular redness, and/or a sensation of tearing) of at least moderate severity
	2-2. VAS score ≥ 40
	2-3. TBUT ≤10 seconds and Schirmer-I test results ≤ 10 mm/5 minutes
	3. Voluntary participation and written informed consent
Exclusion criteria	1. Dry eye symptoms due to eyelid or eyelash defects
	2. Acute infection of the eyelid, eyeball or periorbital area
	3. Skin disease such as Stevens-Johnson syndrome and/or pemphigoid
	4. Vitamin A deficiency
	5. Any external injury to the orbital or periorbital area
	6. A history of eye surgery within the past six months (except refractive surgery)
	7. Impaired blinking due to facial palsy
	8. History of punctal plug or punctal occlusion surgery
	9. Pregnancy, lactation, or plans to conceive
	10. Exclusion at the investigator’s discretion

VAS: Visual analog scale; TBUT: Tear film break-up time.

### Randomization and allocation concealment

For randomization and allocation concealment, a set of random numbers will be generated using computerized SAS block-randomization software (SAS® version 9.3, SAS Institute, Inc., Cary, NC, USA). Sealed, opaque assignment envelopes will be used for allocation concealment [16].

The primary data collected will be used to investigate the impact of expectations on the success of acupuncture treatment. Because participant expectations could affect treatment outcomes, each patient will be queried regarding their perception of acupuncture therapy prior to group allocation [17]: 'How much do you expect that the acupuncture treatment will relieve your dry eye symptoms?’ Participants will be asked to select one point on a 10-point Likert scale (0 not useful to 9 very useful).

## Intervention

### Acupuncture plus usual care group

The acupuncture plus usual care group will be treated three times per week for four weeks. Each session of treatment will include the use of 17 acupuncture points (bilateral BL2, GB14, TE23, Ex1, ST1, GB20, LI4, and LI11, and single GV23). These will be localized according to the 'WHO Standard Acupuncture Point Location in the Western Pacific Region’ protocol [18]. Four experts in the field of alternative medicine who have trained for at least seven years and practiced for at least three years will perform these treatments using 0.20 mm × 30 mm disposable acupuncture needles (Dongbang Acupuncture Inc., Chungnam, Republic of Korea). The '*de-qi*’ sensation will be induced by twisting acupuncture, and the needles will be retained for 20 minutes before removal. The patients will be allowed to use any additional treatment for dry eye symptoms other than punctal plugs or punctal occlusion surgery. Patients will not be permitted to participate in any other regimen of acupuncture therapy. Any changes in medical history or vital signs and reports of adverse events will be recorded at every follow-up visit.

### Usual care control group

The control group will be allowed to use any type of treatment for dry eye symptoms: artificial tear drops, drugs, supplements (for example, cyclosporine, corticosteroids, and autologous serum), and alternative treatments other than those listed above as exclusions. Patients will be followed-up every two weeks and asked to report any change in medical history or drug use at each visit.

### Primary outcome

#### Ocular Surface Disease Index (OSDI)

The primary outcome will be scores on the OSDI, which is a questionnaire consisting of 12 questions for evaluating the effects of dry eye syndrome on vision, ocular symptoms, and any condition associated with dry eye. The patient will answer each question on a scale ranging from 0 to 4, with 0 indicating 'none of the time’ and 4 indicating 'all of the time’. If a certain question is deemed irrelevant, it will be marked as 'not applicable (N/A)’ and excluded from the analysis. The OSDI score is calculated according to the following formula [19]:

$$\mathrm{OSDI}=\frac{\left(\text{Sum}\;\text{of}\;\text{scores}\;\text{for}\;\text{all}\;\text{questions}\;\text{answered}\right)\;\times \;100}{\left(\text{Total}\;\text{number}\;\text{of}\;\text{questions}\;\text{answered}\right)\;\times \;4}$$

The scale ranges from 0 to 100, with higher scores representing more severe cases of dry eye syndrome [20]. This value will be checked during visits 2 (prior to acupuncture treatment), 8, 14, and 15.

### Secondary outcomes

#### Visual Analog Scale (VAS)

The 100-mm VAS is an instrument for the self-assessment of ocular discomfort. Patients will perform these measurements daily for one week. Each participant will mark the level of ocular discomfort (for example, ocular itching, foreign body sensation, burning, pain, and dryness). The VAS score is determined by measuring the distance between the left-hand end of the line and the point marked by the subject. This will be checked during visits 1, 2, 8, 14, and 15. The VAS scores as reported at visit 1 will be used for screening purposes. The VAS scores obtained at visit 2 will be used as baseline for the analysis.

#### Quality of Life (QOL)

The QOL scale is used to measure the effect of dry eye on the patient’s quality of life. The question is posed as follows: 'During the last week, how would rate your quality of life, considering any impact of dry eye symptoms?’ The possible responses range from 0 (excellent) to 6 (worst). This will be measured at visits 2, 8, 14, and 15.

#### Tear Film Break-up Time (TBUT)

The TBUT test assesses tear film stability. Sodium fluorescein (2.5%) is applied to both eyes, and the time that elapses until the first appearance of a dry spot or disruption in the tear film is measured. A single optometrist performed all TBUT measurements, without holding the participant’s eyelid. TBUT results ≤ 10 seconds suggest dry eye of at least moderate severity. The TBUT will be assessed at visits 1 (screening) and 15.

#### Schirmer-I test (with anesthesia)

The Schirmer-I test (with anesthesia) is used to measure baseline tear secretion. After the application of local anesthesia (Alcaine® Alcon, Inc., Texas, USA) to arrest reflex tearing, Schirmer test paper (Color Bar™ Schirmer tear test, Eagle Vision, Inc., TN, USA) is placed in the lateral third of the lower eyelid. With closed eyes, the patient keeps this paper in place for five minutes, after which the length of the wet portion is measured. This measurement will be obtained during visits 1 (screening) and 15. If the Schirmer-I test result is ≤ 10 mm/5 minutes, the patient’s dry eye is of moderate severity or worse.

### Corneal surface photography

Digital photos will be used to evaluate the corneal surface as revealed by fluorescein staining. After dropping one drop of fluorescein 0.25% in each eye, participants will be asked to blink five times to drain any excess dye. The stained corneal surface will be photographed using the cobalt blue filter and yellow filter on the slit-lamp biomicroscope. The results will be graded according to the Oxford scheme (from 0 (absent) to 5 (severe)) and checked during visits 1 and 15 [21].

### Efficacy of drug or other treatment

From visit 14 onward, all participants will be reminded that they can use any sort of treatment except for surgery or acupuncture. Patients will be asked to record any changes in medical history or treatment regimen in a diary. This will be collected for review at the last visit (visit 15).

### General assessment

A general assessment will be carried out in which both practitioners and participants will assess the improvement in symptoms related to dry eye syndrome after acupuncture or the conventional treatment regimen. The patient’s condition will be graded as excellent, good, fair, no change, or aggravated (Table 2).

**Table 2 T2:** Evaluation plan

	**Screening**	**Treatment or observation**												**Assessment**	
**Week**		**1**			**2**			**3**			**4**			**5**^ **a** ^	**13**^ **b** ^
**Visit**	**1**	**2**	**3**	**4**	**5**	**6**	**7**	**8**	**9**	**10**	**11**	**12**	**13**	**14**	**15**
OSDI		**●**						**●**						**●**	**●**
VAS	**●**	**●**						**●**						**●**	**●**
Schirmer-I test	**●**														**●**
TBUT	**●**														**●**
Corneal surface photography	**●**														**●**
QOL		**●**						**●**						**●**	**●**
Drug or therapeutic modalities															**●**
General assessment														**●**	

^a^: 4 weeks after visit 2 + 3 days; ^b^: 12 weeks after visit 2 + 3 days; **●**: All groups.

OSDI: Ocular surface disease index; VAS: Visual analog scale; TBUT: Tear film break-up time; QOL: quality of life.

### Statistical analysis

Because this is an exploratory pilot study designed to evaluate the feasibility of acupuncture for the treatment of dry eye syndrome after refractive surgery, sample size was not calculated according to the conventional power analysis method. Twenty subjects will be recruited for each group.

The statistical analysis will be conducted using SAS software (version 9.3, SAS Institute Inc., Cary, NC, USA) with the significance level set at 0.05. Efficacy measurements were adjusted by intention to treat analysis (ITT). Missing values will be imputed by the last observation carried forward (LOCF) method. Analysis of covariance (ANCOVA) will be used to test measured outcomes (OSDI, TBUT, Schirmer-I test, QOL and VAS for the self-assessment of ocular discomfort). ANCOVA will be used to determine whether dependent variable values are equivalent across levels of a categorical independent variable by statistically controlling for the effects of other variables known as covariates. The change in scores for each group will serve as the dependent variable, the baseline scores will serve as covariates, and the group will serve as the fixed factor. The Chi-square test or Fisher’s exact test will be used to identify any differences among groups in fluorescein staining of the corneal surface.

Using this correlation analysis, we will evaluate the relationship between patients’ expectations of acupuncture treatment and the relief of dry eye symptoms in the acupuncture plus usual care group.

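### LOCF for all missing values sets change to zero on outcomes measured only twice and presumes persistence at week 13; the size, and the direction under unequal dropout, cannot be known from the protocol

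*Protocol article*

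**What the plan says.** Under Statistical analysis, the protocol article states an intention-to-treat analysis and then the missing-data rule: "Missing values will be imputed by the last observation carried forward (LOCF) method". It names no other method and no sensitivity analysis. OSDI, TBUT, Schirmer-I, QOL and VAS are then tested by ANCOVA, where "The change in scores for each group will serve as the dependent variable, the baseline scores will serve as covariates" and group is the fixed factor. Staining is compared by chi-square or Fisher's exact test. The significance level is 0.05.

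The schedule differs by outcome:

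- TBUT: "The TBUT will be assessed at visits 1 (screening) and 15".
- Schirmer-I: "This measurement will be obtained during visits 1 (screening) and 15".
- Staining photographs: "checked during visits 1 and 15".
- OSDI: "This value will be checked during visits 2 (prior to acupuncture treatment), 8, 14, and 15". VAS and QOL have the same analysis visits, with visit 2 as baseline.

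Table 2 agrees. Visit 8 falls in week 3, during treatment. Visit 14 (week 5) is four weeks after visit 2, at the end of the acupuncture course. Visit 15 (week 13) is twelve weeks after visit 2. The section on drug or other treatment rules out acupuncture from visit 14 onward but allows other non-surgical treatment.

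**The concern.** LOCF behaves differently under these two schedules, and neither result is what the analysis is meant to estimate.

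For the outcomes measured twice, there is no intermediate value to carry. A patient without visit 15 keeps the screening value, and for TBUT and Schirmer-I a change of zero enters the ANCOVA as if it had been measured. For staining, the screening grade enters as the week-13 grade.

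For the outcomes measured four times, visit 15 is the only off-treatment assessment, so its purpose is to show whether a benefit lasts. Carrying visit 14 into visit 15 assumes that it does. Patients lost earlier carry their week-3 value or their baseline.

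The outcomes are tested at 0.05, and the Discussion says the pilot will show whether the treatment works and will help set the number of patients for a larger trial. A distorted effect estimate would pass into that calculation.

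**Working it through.** **Inputs from the protocol article:** 20 patients per arm, the visit schedules above, ANCOVA on change with baseline as covariate, and LOCF throughout. It gives no dropout rate, standard deviation, effect size or power, so there is no stated figure to reproduce. All dropout rates, effects, SDs and correlations below are assumptions. Effects are written as improvements, and dropout is taken as unrelated to outcome.

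**1. TBUT and Schirmer-I.** A missing visit 15 gives change = Y1 - Y1 = 0. Let m be the improvement common to both arms, δ the true added effect of acupuncture, and dA and dC the dropout in the acupuncture and control arms. The expected LOCF difference is

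(1 - dA)(m + δ) - (1 - dC)m = (1 - dA)δ + (dC - dA)m.

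*Equal dropout d:* the estimate is (1 - d)δ. Simulated ANCOVA for δ = 0.9 SD, m = 0 (4,000 runs, baseline correlation 0.5):

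| Dropout, both arms | (1 - d) x 0.9 | LOCF, simulated | Observed cases, simulated | Power, LOCF vs observed cases |
|---|---|---|---|---|
| 10% | 0.81 | 0.81 | 0.90 | 0.84 vs 0.86 |
| 20% | 0.72 | 0.72 | 0.90 | 0.75 vs 0.79 |
| 30% | 0.63 | 0.64 | 0.91 | 0.68 vs 0.75 |

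*Unequal dropout, no true effect:* the estimate is (dC - dA)m. With m = 0.8 SD:

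| Acupuncture / control dropout | Formula | LOCF, simulated | Rejection, LOCF vs observed cases |
|---|---|---|---|
| 10% / 30% | +0.16 SD | +0.16 SD | 6.9% vs 4.1% |
| 10% / 20% | +0.08 SD | +0.08 SD | 4.7% vs 5.1% |
| 30% / 10% | -0.16 SD | -0.16 SD | 7.7% vs 5.2% |

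The false effect goes against the arm that loses more patients, and it changes sign when the rates are exchanged.

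**2. OSDI, VAS and QOL, patients lost before any post-baseline visit.** Baseline is carried and the same formula applies. With 5% vs 25% dropout and a common improvement of 10 points, the bias is 0.20 x 10 = 2.0 points. Simulation (SD 20, correlation 0.6) gave about 2 points with rejection near 7%. At 5% vs 15% it gave about 1 point and 5.4%.

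**3. OSDI, VAS and QOL at week 13, visit 14 seen and visit 15 missing.** The estimate is (1 - d) x effect13 + d x effect5. With d = 0.20, effect5 = 10 and effect13 = 3:

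0.80 x 3 + 0.20 x 10 = 2.4 + 2.0 = 4.4.

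If a week-5 effect of 1 unit has gone entirely by week 13, LOCF reports 0.10, 0.20 and 0.30 at 10%, 20% and 30% missing.

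**4. Consequence for sizing a later trial.** Required size varies as 1/effect², with the SD held fixed. Shrinking to 0.8 of the truth multiplies it by 1/0.64 = 1.56. Reading 4.4 for a true 3 multiplies it by (3/4.4)² = 0.46.

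**The case against.** **It is an exploratory pilot, and a separate analysis plan may add more.** Both are fair. The article says that no power calculation was made, and with SD 20 and correlation 0.6 the standard error is about 5 points, so a bias of 1.4 points (4.4 - 3) is small beside the noise. Complete week-13 data would remove the problem. But the rule is stated, not left open, and the article itself gives the results two uses that depend on the effect estimate. This lowers the weight of the point without removing it.

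**LOCF serves intention to treat by keeping everyone in.** It keeps the row but adds no week-13 information. For TBUT and Schirmer-I it adds a zero.

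**OSDI items marked not applicable** are left out of the score by its own formula. The point concerns missed visits only.

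A reader might draw two stronger conclusions, and neither is supported:

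- *That the bias favours acupuncture, because controls are offered nothing new and will leave.* The article gives no dropout figure. The acupuncture arm must attend three times a week for four weeks, while controls are followed every two weeks, so heavier loss in the acupuncture arm is just as arguable. The sign then reverses.
- *That LOCF makes the standard errors too small.* The carried value is a fixed function of each patient's own data, so ANCOVA estimates the variability of the LOCF estimator correctly. With 5% vs 25% dropout, the mean model standard error was 4.88 against an empirical SD of 4.96. Without a common improvement, rejection was 5.2%. The excess near 7% comes from bias alone.

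The loss of power is also modest and depends on the assumptions. For a 0.5 SD effect with 20% missing, it was 37% vs 39% without a common change, and about 31% vs 38% under other assumptions. The shrinkage of about 20% is the stable result.

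**Conclusion.** The point stands in a limited form. Read with the article's own schedule, the LOCF rule does three things:

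- It sets TBUT and Schirmer-I change to exactly zero, and carries the screening staining grade, for anyone without visit 15.
- It gives a false effect of (dropout difference) x (common improvement) when the arms lose different numbers of patients.
- It pulls the week-13 OSDI, VAS and QOL effects towards the end-of-treatment effects.

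The first and third follow from the schedule alone once a visit is missed. Their size depends on dropout, which is not given. At 20% missing (4 of 20 per arm), the TBUT and Schirmer-I effects lose a fifth of their value, and a week-13 effect of 3 reads as 4.4 if the week-5 effect is 10. The direction under unequal dropout cannot be known from the article. The change should be made, but the trial does not fail without it.

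**What to change.** Replace LOCF as the main method and keep it only as a sensitivity analysis.

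- **OSDI, VAS and QOL:** a mixed model for repeated measures on weeks 3, 5 and 13, with baseline, arm, visit and arm-by-visit interaction, and no imputation. Patients with no post-baseline visit do not contribute; report their number by arm.
- **TBUT and Schirmer-I:** ANCOVA on observed week-13 values with the baseline covariate.
- **Staining:** the planned test on observed week-13 grades.

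Multiple imputation fitted separately by arm is not a good substitute for the tear outcomes, because about 16 patients per arm would support each model. In a simulation with 20% missing, a 0.5 SD effect and an assumed sign-symptom correlation of 0.2, it raised the standard error from 0.29 (observed cases) to 0.41 and cut power from 41% to 21%.

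The cost is analysis wording and a little code in the SAS software already named, with no new visits or data. Intervals become somewhat wider. With assumed SD 20 and correlation 0.6, the residual SD is 20 x √(1 - 0.36) = 16. At 20% missing, the observed-case standard error is 16 x √(2/16) = 5.7, against 4.8 to 5.1 for LOCF in simulation. The replacement also assumes that data are missing at random given what is modelled, and the plan should say so.

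### The ordered 0–5 Oxford staining grade is given a chi-square or Fisher test that, as described, uses neither its order nor the screening grade: an avoidable loss of efficiency on a non-primary outcome

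*Protocol article*

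**What the plan says.** All references are to the protocol article.

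- **Outcome.** Under Corneal surface photography: "The results will be graded according to the Oxford scheme (from 0 (absent) to 5 (severe)) and checked during visits 1 and 15". Table 2 confirms both time points for all groups. Visit 1 is screening and visit 15 is week 13.
- **Planned test.** Under Statistical analysis, staining is assigned to a chi-square or Fisher's "exact test will be used to identify any differences among groups in fluorescein staining of the corneal surface". No ordering, cut-point, change category or baseline term is mentioned.
- **Other outcomes.** The same paragraph applies ANCOVA to five named outcomes: "OSDI, TBUT, Schirmer-I test, QOL and VAS for the self-assessment of ocular discomfort". In that model, "the baseline scores will serve as covariates, and the group will serve as the fixed factor". QOL is one item with ordered responses from 0 to 6.
- **Size and level.** "Twenty subjects will be recruited for each group", tested "with the significance level set at 0.05". As a pilot, "sample size was not calculated according to the conventional power analysis method".

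**The concern.** A chi-square or Fisher test on a table of grades by arm treats the grades as unordered labels: relabel them in any order and the p-value is unchanged. The test spreads its power over every possible pattern of difference, when the pattern of interest is a shift towards lower or higher grades. It also leaves out the screening grade, which the trial collects anyway and which should predict the week-13 grade.

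The choice is also hard to square with the rest of the paragraph. QOL, an ordered item with seven levels, gets a baseline-adjusted comparison. Staining, an ordered grade with six levels, does not, and no reason is given.

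Two things are at stake. First, the comparator is usual care without a sham procedure, and OSDI, VAS and QOL are self-reported; staining is one of three ocular-surface measures that depend less on expectation. Second, the Discussion says the results should help to size a later trial. A test of general association gives no directional effect estimate or interval to plan from.

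**Working it through.** **No figure to reproduce.** The article states no power or sample-size figure for staining, so the check is a simulation under stated assumptions.

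**Inputs from the article.** 20 per arm; significance level 0.05 (sidedness not stated, two-sided assumed); grades 0–5 at screening and week 13.

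**Assumed inputs.** One grade per participant and all 40 participants analysed. Grades are cut from a latent bivariate normal, with a treatment shift of 0.5, 0.8 or 1.0 SD and a baseline–follow-up correlation of 0.3, 0.5 or 0.7. Four distributions over grades 0 to 5 were used, in %: spread (10/20/25/20/15/10), mild (25/35/25/10/4/1), uniform, and concentrated (40/40/15/5/0/0). There were 1,500 simulated trials per setting.

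**Step 1: is chi-square usable?** Expected count in a cell = 20 × (participants with that grade) / 40 = half the grade total. It reaches 5 only if at least 10 of the 40 participants have that grade.
- Six grades occupied: at most three can hold 10 or more, so at least 3/6 = 50% of cells fall below 5.
- Five grades occupied: at most three can, so at least 2/5 = 40% fall below 5.
- Four grades occupied: only an exact 10/10/10/10 split avoids it; otherwise at least 1/4 = 25% fall below 5.
- Three or fewer: chi-square can be tenable.

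Fisher would therefore usually, though not certainly, be the working test.

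**Step 2: power at shift 0.8 SD, correlation 0.5.** Relative loss = 1 − (power of planned test) / (power of ANCOVA on screening grade).

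| Distribution | Chi-square | Fisher | Wilcoxon | ANCOVA | Loss, chi-square | Loss, Fisher |
|---|---|---|---|---|---|---|
| Spread | 0.324 | 0.360 | 0.617 | 0.739 | 56% | 51% |
| Mild | 0.332 | 0.397 | 0.599 | 0.683 | 51% | 42% |
| Uniform | 0.356 | 0.382 | 0.637 | 0.729 | 51% | 48% |
| Concentrated | 0.349 | 0.409 | 0.535 | 0.616 | 43% | 34% |

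Example: spread, Fisher, 1 − 0.360/0.739 = 0.51.

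**Step 3: the full range.**
- Shift 0.8 SD, all correlations: chi-square 0.32–0.36, Fisher 0.36–0.41, ANCOVA 0.56–0.85. Loss about 40–60% (chi-square) and 32–55% (Fisher).
- Shift 0.5 SD: loss about 38–72%. The largest is chi-square, spread, correlation 0.7: 1 − 0.139/0.501 = 0.72.
- Shift 1.0 SD: loss about 26–48%. The smallest is Fisher, concentrated, correlation 0.3: 1 − 0.563/0.757 = 0.26.
- Ignoring order alone, with Wilcoxon as comparator at 0.8 SD, costs roughly 24–49%.

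**Step 4: other readings of the table, at 0.8 SD.**
- Near-median split with Fisher: power 0.34–0.39, no better than the full grade table.
- Improved/unchanged/worse, with grades cut at −1.5, −0.7, 0, 0.7 and 1.5 on the latent scale: 0.62 against 0.87 for ANCOVA at correlation 0.7 (1 − 0.62/0.87 = 29% loss), and 0.44 against 0.75 at correlation 0.5 (41% loss).
- A further simulation over three distributions and correlations 0.3–0.7 gave 0.23–0.65 for the change table, 0.27–0.36 for chi-square on the week-13 grade and 0.45–0.89 for the adjusted analysis. Because 0.23 lies below the chi-square minimum of 0.27, the change table is not better in every setting.

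**Step 5: cross-check and validity.** Noncentrality = 20 × 0.8² / 2 = 6.4. Asymptotic power is 0.46 on 5 df and 0.72 on 1 df. With baseline at correlation 0.5, noncentrality is 6.4/(1 − 0.25) = 8.53 and 1-df power is 0.83; loss 1 − 0.46/0.83 = 45%. With no effect, rejection was 0.03–0.04 (chi-square), about 0.04–0.05 (Fisher) and about 0.04–0.06 (Wilcoxon, ANCOVA), so the gain does not come from inflated error.

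**The case against.** The strongest reply is that the article does not say which table is tested. It could hold the week-13 grade, a dichotomy, or change categories, and an article commonly leaves such detail to a fuller document. That stands as a limit on the size of the loss. It does not remove the point: the family of test is stated, a dichotomy does no better, and a change table uses the screening grade only coarsely and usually still loses power.

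It is also fair that this is a non-primary outcome in an exploratory pilot with no power calculation. Even the better analysis has limited power at small effects: at 0.5 SD the ANCOVA power was 0.29–0.50. That stands and sets the weight of the point.

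Some stronger inferences are tempting but not supported:
- **Half the power is lost.** No single figure follows, since the article gives no effect size, grade distribution or correlation. Entry criteria set no staining threshold, so low grades may predominate, and there the loss is smaller.
- **Staining is the only outcome left unadjusted.** The general assessment is not in the ANCOVA list either and has no baseline measurement in Table 2. The contrast is with the five listed outcomes.
- **A 2 × 6 Fisher test is certain.** It depends on how many grades are occupied and on the table chosen.
- **A significant result would leave direction unknown.** That is true of the p-value alone; the grades by arm would show it.

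**Conclusion.** The point holds as a matter of efficiency. As described, the planned test uses neither the order of a six-level grade nor its collected screening value, while a comparable ordinal item in the same paragraph is baseline-adjusted. Against a baseline-adjusted analysis, the relative power loss is roughly 25–70%, centrally about 35–55%. These figures rest on assumed shifts of 0.5–1.0 SD, correlations of 0.3–0.7, the four grade distributions above, and 20 analysed per arm with one grade each. The loss is smallest when the effect is large, grades sit in few categories and the correlation is low. With change categories it is smaller at moderate to high correlation, but usually still present.

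A reader might infer that the staining comparison is invalid. It is not: neither bias nor inflated type I error results. The point is minor, and worth taking because the improvement is free.

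**What to change.** Replace the chi-square/Fisher sentence with one prespecified, baseline-adjusted ordinal analysis of the week-13 grade. Either of these would do, chosen before the comparison is seen:

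- proportional-odds regression of the week-13 grade on arm, with the screening grade as covariate, reporting the common odds ratio with a 95% CI; or
- adding staining to the existing ANCOVA list, handled as QOL is, reporting the adjusted mean difference with a 95% CI.

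Keep the table of grades by arm as description, so that the direction and pattern remain visible. If the sponsor prefers to retain a categorical test, the text should at least say which table is tested: week-13 grade, a dichotomy, or change categories.

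The cost is one sentence. No new data are needed, because the screening grade is already collected.
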